### Electrocardiogram Device

The ECG patch used is the AT-Patch from ATsens Co, Ltd (Seongnam-si, Republic of Korea), which is a single-channel ECG. The AT-Patch carries the CE mark as a registered medical device and is available for sale in the European Union. It can easily be attached to the chest and continuously records the heart rhythm for 14 days. During monitoring, patients can observe their ECG via an app (AT-Note) and may indicate symptoms (eg, dizziness or palpitations) via this app. Live tracking by the study physician is not possible. The ECG patch is light and compact and meets the grade of being showerproof (IP44/IP57). At the end of the monitoring period, the patient sends back the patch for rhythm evaluation. The detected arrhythmias are documented and adjudicated by two independent physicians.

Figure 2 shows a schematic representation of the ECG patch on the chest and an example rhythm analysis of the accompanying app.

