## Methods

### Study Design

The Hypertrophic Cardiomyopathy: Clinical Impact of a Prolonged mHealth-Based Arrhythmia Monitoring by Single-Channel ECG (HCM-PATCH) study aims to investigate the association between the occurrence of cardiac arrhythmias with detected gene mutations and the extent of late gadolinium enhancement in cMRIs. This single-center prospective cohort study will be conducted at the Department of Cardiology and Intensive Care Medicine at the University Hospital Ostwestfalen-Lippe (OWL), Campus Klinikum Bielefeld in Germany. The trial is registered under clinical trial number DRKS00032144 (DRKS-ID).

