### Recruitment

According to the sample size calculation (see Statistical Analysis section), recruiting 34 patients will be sufficient for the statistical analysis. Study participants will receive an echocardiography at rest and during exercise (bicycle ergometry) and a cMRI. In addition, their symptoms, family history, and premedication are collected, and their HCM Risk–SCD calculator score will be calculated. According to this score, patients are allocated to three risk groups: low risk (<4%), intermediate risk (4%-6%), and high risk (>6%) of SCD within 5 years. An ICD is generally recommended in the high-risk group, should be considered in the intermediate-risk group, and is not indicated for the low-risk group [1]. For this study, it is planned to recruit 17 patients with low and 17 with intermediate risk scores. All these patients will receive the 14-day ECG patch.

Patients with HCM between the ages of 18 and 75 years will be included if they have not yet undergone implantable loop recorder, pacemaker, or ICD implantation and if their estimated 5-year SCD risk according to the HCM Risk–SCD calculator score is <6%. A maximum age of 75 years was set as the upper limit, as SCD in patients with HCM mainly occurs at a young age [13]. Patients with a pre-existing cardiac implant (pacemaker, ICD, or implantable loop recorder) or an already accepted indication for it; Morbus Parkinson disease with relevant tremor; a transcoronary ablation of septal hypertrophy procedure in the last 4 weeks; inability to give informed consent; and current symptoms or a history of skin cancer, rash from skin adhesive, or dermatoses (contraindication to wearing the patch) are excluded.

A therapeutic procedure is established for the patient based on the information available to date. Afterward, an ECG patch is applied to the chest to continuously monitor the heart rhythm over 14 days. After completing the 14-day wearing period, patients should return the ECG patch. Any arrhythmias recorded will then be documented, and the therapeutic procedure will be re-evaluated with a recalculation of the HCM Risk–SCD calculator score.

An overview of the study process can be seen in Figure 1.

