We hypothesize that prolonged rhythm monitoring will detect more arrhythmias than 24- or 48-hour monitoring. In a study with prolonged rhythm monitoring by Holter ECG over 14 days, 75% of patients with HCM had nsVT, compared with only 16.9% of patients in the first 24 hours [6]. However, it remains unclear if all these patients with nsVT should now receive an ICD. Previous studies have shown that patients who present with nsVT during 24-hour monitoring show it more frequently if monitoring is prolonged. Patients who showed nsVT later in the subsequent 14 days usually had only one episode [7]. Thus, it can be speculated that the detection of nsVT in a 24-hour monitoring period indicated more frequent spells of nsVT overall, with an associated higher SCD risk. Moreover, the rate and duration of nsVT vary, suggesting that longer and more rapid nsVT episodes indicate a higher SCD risk [6]. Prolonged monitoring may allow for the identification of patients with more frequent nsVT episodes, also taking into account the rate and duration of nsVT.

In addition, a correlation with late gadolinium enhancement load on cMRI will be investigated. If patients with high late gadolinium enhancement load show increased nsVT, these scar areas detected on cardiac MRIs could be identified as possibly pathogenic for the arrhythmias, and appropriate therapy (eg, ICD fitting) should be performed. This has so far not been investigated, so the results are needed.

In addition, the mHealth ECG patch method used here offers opportunities for other diseases as well. For example, patients with a stroke of unclear origin can be screened for AF over an extended period. It is also possible to capture intermittent subjectively perceived cardiac arrhythmias with the help of such an ECG patch, as this is often not possible with normal long-term ECGs.

In summary, prolonged mHealth-based rhythm monitoring will be used to investigate arrhythmia burden in patients with HCM. Increased detection of arrhythmias compared with 24-hour long-term ECG monitoring can be expected. It is essential to individually consider the rhythm monitoring results and optimize therapy accordingly. Findings of prolonged rhythm monitoring might be helpful in cases of borderline risk. A thorough discussion of the findings and possibly individual reassessment using the risk calculator could be an approach.

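### No masking is stated for the two arrhythmia adjudicators, although risk score and cMRI are obtained in the same department before the patch is read; coded reading would be a cheap safeguard

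*Protocol article*

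**What the plan says.** **Reading.** The Electrocardiogram Device section describes the patch as a device "which is a single-channel ECG" and notes that "Live tracking by the study physician is not possible", so reading follows the return of the patch. The safeguard it gives is: "The detected arrhythmias are documented and adjudicated by two independent physicians". The article does not explain whether independent means of each other or of the clinical team, and no section mentions masking either way.

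**What is known beforehand.** In the Recruitment section, echocardiography, cMRI, history and the HCM Risk–SCD score come first: "According to this score, patients are allocated to three risk groups". A therapeutic plan is set, and only then is the patch applied. After its return, "Any arrhythmias recorded will then be documented, and the therapeutic procedure will be re-evaluated with a recalculation of the HCM Risk–SCD calculator score". All of this takes place in one department (Study Design). The timing of the genetic result is not given.

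**What is compared.** The Study Design section says the study is to "investigate the association between the occurrence of cardiac arrhythmias with detected gene mutations and the extent of late gadolinium enhancement in cMRIs", and the Results section lists arrhythmia prevalence with positive cMRI and with positive genotype as secondary end points. The Statistical Analysis section sizes the study on low versus intermediate risk (25% versus 75%). The Outcomes section compares the first 24 and 48 hours with the whole 14 days, and the Discussion states the expected direction: "We hypothesize that prolonged rhythm monitoring will detect more arrhythmias than 24- or 48-hour monitoring".

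**The concern.** The nsVT definition in the Outcomes section fixes a beat count, a rate and a maximum duration. It does not settle whether three beats on a single channel are ventricular, aberrantly conducted or artifact. That call is left to the adjudicators, and one accepted run is enough to make a patient positive.

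A reader who knows that a patient is at intermediate risk, or has extensive enhancement, may accept a doubtful run more readily. Two readers who both hold that knowledge do not cancel the effect, even if they are independent of each other. At stake is differential misclassification in the risk-group, cMRI and genotype comparisons and, through the recording day, an inflated estimate of what days 3 to 14 add.

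**Working it through.** **1. Order of information.** Taken together, the Recruitment and Study Design sections put the risk score, the cMRI and the treatment plan in the department before the recording is read. The Data Protection section keeps the recordings in the hospital network and aims pseudonymization at outsiders. Nothing described would keep the risk data from the readers, and nothing says that they have them.

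**2. The plan's own figure.** Inputs from the Statistical Analysis section are 25% versus 75%, α = 0.05 (taken as two-sided) and power 0.80.

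n per group = [1.960·√(2·0.5·0.5) + 0.842·√(0.25·0.75 + 0.75·0.25)]² / (0.75 − 0.25)² = (1.386 + 0.515)² / 0.25 = 14.5, rounded up to 15.

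That gives 30 in total, and 30 / 0.9 = 33.3, rounded up to 34. The stated 30 and 34 reproduce, and masking does not enter them.

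**3. One patient.** 1/15 = 6.7 percentage points for that group's prevalence. One patient in each group, in opposite directions, moves the difference by 2/15 = 13.3 points. A single run has this effect only if the patient has no other accepted run.

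**4. At the planned effect.** Uncorrected two-sided χ² test, 15 per group. The pooled proportion is 0.5 in both cases, so SE = √(0.25·2/15) = 0.1826.
- 4/15 versus 11/15 (nearest to 25% and 75%): difference 0.467, z = 2.56, p = 0.011.
- 5/15 versus 10/15: difference 0.333, z = 1.83, p = 0.068.

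One changed classification per group crosses 0.05. The χ² test is the one used for sizing; the planned primary analysis is a Poisson regression, so these p-values show fragility and do not predict the final result.

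**5. Assumed reading error.** The documents give no error rate, so d below is an assumption. Suppose both groups have the same true prevalence p, with 15 per group. One way: a share d of true negatives is called positive in the intermediate group only, giving p + (1 − p)d. Both ways: in addition, the same share of true positives is missed in the low-risk group, giving p(1 − d). Rejection rates from the exact binomial distribution are:

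| d | p = 25%, one way | p = 25%, both ways | p = 50%, one way | p = 50%, both ways |
|---|---|---|---|---|
| 0 | 5.4% | 5.4% | 4.6% | 4.6% |
| 5% | 6.1% | 6.6% | 4.8% | 5.4% |
| 10% | 7.9% | 10.0% | 5.4% | 7.8% |
| 20% | 14.6% | 23.3% | 7.9% | 18.3% |

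The effect runs from negligible to serious, depending wholly on d.

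**6. The within-patient comparison.** The 24- and 48-hour windows lie inside the 14-day recording. Everyone positive by 48 hours is also positive by 14 days, so the number of patients detected cannot fall, whoever reads. The gain is the share whose first accepted run comes after the short window. Lenient reading of late runs would enlarge that share but could not change its sign.

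**The case against.** The strongest objection is that silence is not a defect. This is a condensed article, the full protocol may specify masking, and nothing in the text is contradicted. The adjudicators may not be the treating physicians, and genetic testing is not listed in the work-up before the patch. This stands. A reader might infer that adjudication is unmasked, with the answer in view; the document does not say so.

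A second tempting reading is that every comparison in the study is biased toward its hypothesis. That fails as well:
- The windows are nested, so the direction of the 14-day gain is fixed.
- For enhancement the Discussion speaks only conditionally, and for genotype it states no direction.
- The low- versus intermediate-risk contrast appears in the sample size calculation, while the primary end point takes the two groups together.
- Three secondary end points are plain patient counts.

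The 15-per-group arithmetic would hold for any binary outcome and is not evidence of bias. Nor are the cMRI and genotype subgroup sizes given. The Discussion's remark that later-detected patients usually had one episode reports a previous study, so it cannot be taken as describing this cohort.

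Two readers and a rule-based definition do limit discretion. Reading anonymous strips pooled across patients would also cost the reader each patient's own baseline morphology, which matters on one lead.

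What remains is that the article does specify how the endpoint is read, by number and independence of readers. Adding masking would be better than the method as stated.

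**Conclusion.** The point holds as a cheap improvement to the stated reading method, not as a demonstrated error. No figure in the article changes. The exposure lies in the risk-group, cMRI and genotype comparisons and in the size of the 14-day gain.

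The quantified sensitivity is 6.7 points per reclassified patient in a risk group. At the planned effect, one reclassified patient in each group moves p from 0.011 to 0.068. This assumes 15 evaluable patients per group and the χ² test used for sizing. The actual bias depends on a reading error that the document does not give, and on whether the readers in fact see the risk data, which it does not say.

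**What to change.** State in the protocol that:
- the same two physicians read the recordings under a study code, masked to risk group, cMRI and genotype;
- where practicable, the recording day is hidden on the candidate strips, while a reference strip of the patient's own baseline rhythm is kept;
- their calls are locked before the score recalculation and the therapy re-evaluation;
- urgent findings are handled outside this process.

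If the full protocol already provides for masking, one sentence saying so is enough.

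The cost is minor relabelling work for 34 recordings, more if many strips are extracted from each, and a short delay before re-evaluation. The readers stay the same. At the time of writing, 26 of 34 patients were recruited and data analysis had not started. Because recordings are stored, those of patients already enrolled could still be read this way, although a reader may recall some cases.

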**Figure 2 figure2:**
[figure not shown]
Single-channel electrocardiography system in situ and sample screen of the accompanying app.

### Outcomes

The rate of nsVT detection in the first 24 and 48 hours of monitoring versus the whole 14-day monitoring period will be compared. In addition, the prevalence of AF and other arrhythmias will be examined. Moreover, the results of the cMRI and, if applicable, the results of the genetic examination will be considered. The HCM Risk–SCD calculator score will be recalculated if new findings have occurred.

nsVT is defined as ≥3 consecutive ventricular beats at a rate of 120 beats per minute, lasting for <30 seconds [1]. AF is defined as atrial tachyarrhythmia lasting for >30 seconds [15]. The diagnosis of HCM is based on echocardiography; septum hypertrophy ≥15 mm in the absence of other causes of myocardial hypertrophy or septal or posterior wall thickness ratio >1.3 is required.

At the patients’ request, they will be informed about the rhythm-monitoring results and the resulting therapy changes after the ECG patch has been returned.

### Statistical Analysis

The sample size has been planned in collaboration with the Department of Biostatistics and Medical Biometry at the Medical School OWL, Bielefeld University. Patients should be divided into low- or intermediate-risk groups according to their HCM Risk–SCD calculator score, and both groups should be of equal size. Based on the prevalence of nsVT, an assumption was made for the group of low-risk patients based on the publications of Magnusson and Mörner [16] and Sakhi et al [17], where the prevalence after a 24- to 48-hour long-term ECG ranged from 7% to 42%. For case-finding purposes, the assumption was made that a similar increase (ie, a doubling) would be expected after 14 days in the intermediate-risk group. Therefore, a prevalence of 25% after 14 days is assumed. In the intermediate-risk group, a prevalence of 75% is expected [6]. Using a *χ*^2^ test, the total number of cases is 30, corresponding to 15 patients per group (α=0.05, power=0.8). In addition, a dropout probability of 10% was considered. This would result in 34 cases (17 per group).

After data collection, a statistical analysis will be conducted concerning the primary and secondary end points. Since this is a cohort study, all analyses will be adjusted for confounders, including, for example, age and sex. Potential confounders will be assessed from a clinical point of view before the statistical analysis is performed. A Poisson regression will be applied to analyze the primary end point (rate of nsVT detection). Furthermore, we will conduct a negative binomial regression as a sensitivity analysis. The same will be done for the secondary end points measured as the number of patients that experience specific events during the study period. Secondary end points regarding the prevalence of cardiac arrhythmias will be analyzed using logistic regression.

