## Introduction

Cardiac arrhythmias, especially nonsustained ventricular tachycardia (nsVT) and atrial fibrillation (AF), are important comorbidities of hypertrophic cardiomyopathy (HCM) [1,2]. In particular, nsVT is a predictor of sudden cardiac death (SCD) [3,4]. A well-established risk assessment is the HCM Risk–SCD calculator, which queries, among other parameters, the occurrence of nsVT. It is used for recommendations regarding the primary prophylactic implantation of an implantable cardioverter-defibrillator (ICD) [4].

Therefore, adequate screening for nsVT in patients with HCM is highly relevant. It must be assumed that more intensive monitoring can increase the detection rate of cardiac arrhythmias. For example, in one study, a 14-day long-term Holter electrocardiography (ECG) detected nsVT in up to 75% of intermediate-risk patients with HCM. In the same group, a 48-hour long-term ECG revealed nsVT in only 34% of patients [5,6]. In addition, a trial of 100 patients with HCM in Spain showed a 62% rate of nsVT during 30 days of monitoring compared to 8% in the first 24 hours [7]. In another study, 24- to 48-hour long-term Holter ECGs showed at least one AF episode in 23% of patients with HCM [8]. It can be speculated that prolonged ECG monitoring may increase AF detection, leading to the earlier introduction of oral anticoagulants to prevent embolic complications. Patients with HCM with AF have an exceptionally high risk of embolic complications [1].

The feasibility of mobile health (mHealth)–based screening for arrhythmias has not yet been thoroughly investigated in patients with HCM. Holter long-term ECGs and implantable loop recorders are established in everyday clinical practice. Whereas prolonged Holter monitoring is associated with patient discomfort, implantable devices are expensive, have some limitations concerning specificity in arrhythmia detection [9], and carry a risk of surgical intervention for implantation and explantation. More recently, mHealth ECG recorders have become increasingly available, and thus, it should be investigated to what extent mHealth-based prolonged ECG monitoring is feasible and accepted by patients.

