### Questionnaires

At the beginning of study recruitment, various data such as the patient’s family history, previous syncope or rhythm abnormalities will be collected. In addition, secondary causes for left ventricular hypertrophy, such as arterial hypertension, will be queried. At the beginning and after monitoring completion, we will also ask patients if they have any questions, concerns, or requests they want to address with us. After completion of the 14-day monitoring period, the patient’s perception of the mHealth measure will be evaluated through a questionnaire (Multimedia Appendix 1). This questionnaire is based on the System Usability Scale by Brooke [14], a standardized questionnaire for evaluating utensils.

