## Discussion

This prospective study aims to measure the prevalence of nsVT in 34 patients with HCM observed by mHealth-based continuous rhythm monitoring over 14 days compared to standard practice (a 24- and 48-h long-term ECG). Thereby, the frequency of ventricular arrhythmias in the 14 days is compared with the frequency in the first 24 or 48 hours for the same patient (intraindividual comparison). We will evaluate whether the prolonged rhythm monitoring detects nsVT and AF more often compared to conventional 48-hour monitoring and to what extent these findings can induce changes in therapeutic management. It may be speculated that, especially in patients with intermediate HCM Risk–SCD calculator scores, prolonged monitoring may identify patients at high risk, who may potentially benefit from a prophylactic ICD, with higher accuracy. If no rhythm abnormality is detected during the 14-day monitoring, this will not likely occur in everyday life and ICDs can be avoided due to a sufficiently low risk. In addition, a higher diagnostic yield for previously undetected AF may also improve decision-making regarding the need for early anticoagulant therapy.

We set an upper age limit of 75 years because it is known that especially young patients with HCM especially have a higher risk of SCD [13]. Nevertheless, a residual risk remains, so no upper limit for ICDs is defined in the European Society of Cardiology guidelines. Several years ago, the DANISH (The Danish Study to Assess the Efficacy of ICDs in Patients With Nonischemic Systolic Heart Failure on Mortality) study demonstrated no survival benefit from an ICD in patients older than 75 years in a sample of patients with systolic heart failure [18]. We have followed this age limit despite the different patient samples.

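### Patients with known nsVT or AF may enrol and no end point separates them, so known AF counts as detected by the patch and any low- versus intermediate-risk contrast in nsVT is partly built in

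*Protocol article*

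**What the plan says.** **Grouping.** The Introduction describes the HCM Risk–SCD calculator as a tool "which queries, among other parameters, the occurrence of nsVT". Under Recruitment, the score obtained before the patch is applied defines three classes, "low risk (<4%), intermediate risk (4%-6%), and high risk (>6%) of SCD within 5 years", and 17 patients are planned in each of the two lower ones. Statistical Analysis starts from the same split: "Patients should be divided into low- or intermediate-risk groups according to their HCM" Risk–SCD score.

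**Sizing.** For the low-risk group: "Therefore, a prevalence of 25% after 14 days is assumed". For the other: "In the intermediate-risk group, a prevalence of 75% is expected". With a χ² test, "the total number of cases is 30, corresponding to 15 patients per group (α=0.05, power=0.8". A 10% dropout allowance raises this to 34.

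**Eligibility.** Recruitment excludes implanted devices or an accepted indication for one, Parkinson disease with tremor, a recent septal ablation, inability to consent, and skin conditions. Neither earlier nsVT nor earlier AF is on the list.

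**Baseline history.** Under Questionnaires, "previous syncope or rhythm abnormalities will be collected". No group, end point or model in the article uses this item. Age and sex are the only confounders named, as examples.

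**End points.** The Results section makes nsVT prevalence the primary end point. One secondary end point counts patients in whom prolonged monitoring finds AF longer than 30 seconds. Neither is limited to patients without the arrhythmia beforehand. The Discussion gives a narrower reason for looking for AF: "a higher diagnostic yield for previously undetected AF may also improve decision-making".

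**The concern.** The clinical value of longer monitoring lies in what was not known before. As written, the counts mix patients in whom the patch can add a diagnosis with patients in whom it cannot.

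- **AF.** A patient enrolled with known AF who has AF on the patch is counted as a detection. The end point then does not measure what the Discussion argues for.
- **nsVT and the score.** If nsVT was already entered in the baseline score, a patch nsVT cannot change that item. Such patients dilute any statement on score reclassification. If their nsVT first appears on the patch after 48 hours, it still counts as a gain from prolonged monitoring, although it tells the clinician nothing new on that item.
- **Low versus intermediate risk.** Prior nsVT raises the score and so makes the intermediate group more likely. The Discussion itself reports that patients with nsVT on 24-hour monitoring show it more often when monitoring is prolonged. Part of any difference in patch nsVT between the groups therefore follows from how they were formed.

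**Working it through.** **1. The plan's own figure.** Inputs: 25% and 75%, two-sided α = 0.05 (sidedness is not stated; two-sided reproduces the figure), power 0.80, pooled proportion 0.50.

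n per group = [1.96·√(2·0.5·0.5) + 0.8416·√(0.25·0.75 + 0.75·0.25)]² / 0.50² = (1.386 + 0.515)² / 0.25 = 14.5, so 15 per group and 30 in total. With dropout, 15/0.9 = 16.7, so 17 per group and 34 in total. The stated size reproduces; no arithmetic error is alleged.

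**2. Proxies for known nsVT.** The share of enrolled patients with known nsVT is not given. The short-ECG rates in the article are used as assumed stand-ins:

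- Intermediate risk: 34% (48 hours, Introduction) or 16.9% (first 24 hours, Discussion).
- Low risk: 7% (lower end of the 7% to 42% range in Statistical Analysis) or 12.5%. The latter is not in the article; it is 25% halved, reading the 14-day rate as a doubling. Values above 25% cannot be used, because they exceed the assumed 14-day rate.
- All known nsVT is assumed to recur on the patch.

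**3. What grouping alone could produce.** Suppose patients without known nsVT have the same 14-day rate of 20% in both groups (an assumption). Patch prevalence = known + (1 − known) × 0.20.

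- Intermediate, 34% known: 0.34 + 0.66 × 0.20 = 47.2%
- Low, 7% known: 0.07 + 0.93 × 0.20 = 25.6%, gap 21.6 points
- Low, 12.5% known: 0.125 + 0.875 × 0.20 = 30.0%, gap 17.2 points

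To reach 75% in the intermediate group this way, with certain recurrence, the known share would have to be (0.75 − 0.20)/(1 − 0.20) = 69%, about twice the higher proxy.

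**4. What remains under the plan's own rates.** Rate among patients without known nsVT = (total − known)/(1 − known).

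| Known, intermediate | Known, low | Rate, intermediate | Rate, low | Gap (points) |
|---|---|---|---|---|
| none removed | none removed | 75% | 25% | 50 |
| 34% | 12.5% | 0.41/0.66 = 62.1% | 0.125/0.875 = 14.3% | 48 |
| 34% | 7% | 62.1% | 0.18/0.93 = 19.4% | 43 |
| 16.9% | 7% | 0.581/0.831 = 69.9% | 19.4% | 51 |
| 16.9% | 12.5% | 69.9% | 14.3% | 56 |

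In the 34% and 12.5% case the odds ratio goes from (0.75/0.25)/(0.25/0.75) = 9 to (0.41/0.25)/(0.125/0.75) = 9.8.

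**5. AF.** The Introduction gives AF in 23% of patients with HCM on 24- to 48-hour Holter. Then 0.23 × 30 = 6.9 and 0.23 × 34 = 7.8, so about 7 or 8 patients could count as detected although a short ECG would already have shown their AF. This is an illustration, not an upper bound.

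**The case against.** A reader might infer that the group comparison is circular and biased upward as evidence that the score predicts nsVT. The documents do not support that.

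- The article never claims to test whether the score predicts nsVT. Low versus intermediate risk appears in recruitment and sizing, not in the list of end points. The stated objective is the within-patient comparison of 24 or 48 hours with 14 days, which does not depend on how the groups were formed.
- The overlap is partial. nsVT is one of several inputs, and the grouping uses prior nsVT, not the patch recording.
- Under the plan's own rates, removing known cases hardly narrows the gap and in some settings widens it (step 4). The 17 to 22 points in step 3 need an equal-rate assumption that is not in the article.
- Prevalence properly includes recurrent arrhythmia. The therapy-change end points count only changes caused by the detected arrhythmia, so they are less exposed. The score is recalculated only when there are new findings.
- Known arrhythmia may be less common than the proxies suggest. The Abstract says long-term ECG is rarely performed in routine practice, and the score limit and device-indication exclusion may remove some patients with known nsVT.
- Confounders are to be chosen before analysis, so prior nsVT could be one of them in an analysis plan that is not shown.

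All of this stands, and it limits the point. It does not remove it: eligibility and end-point wording are fixed in the article, and adjusting for prior nsVT would not turn the AF end point into newly detected AF.

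**Conclusion.** The point holds in a limited form. The clearest part is AF: the end point counts any AF on the patch, while its rationale is AF not known before. For nsVT, the all-patient prevalence and the within-patient comparison are legitimate, but they do not show how much new information the patch gives, and known cases dilute any reclassification result.

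A low- versus intermediate-risk contrast in nsVT is partly built in, by an amount that the article does not allow one to fix. It could be 17 to 22 points if patients without known nsVT have equal 20% rates. Under the plan's 75% versus 25%, the gap left after removing known cases is 43 to 56 points, against 50 planned. These figures assume that short-ECG rates stand for known nsVT at enrolment and that known nsVT always recurs. They show that the contrast should not be read as evidence that the score predicts nsVT. They do not show that the planned contrast is an artefact.

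**What to change.** Keep the all-patient nsVT prevalence and the within-patient comparison of 24 or 48 hours with 14 days. From the baseline history, classify each patient as with or without known nsVT, and with or without known AF. Then add:

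- AF detection among patients without known AF;
- 14-day nsVT yield and score reclassification among patients without known nsVT;
- the same results for patients with the known arrhythmia, shown separately.

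Stratify or adjust any low- versus intermediate-risk comparison of nsVT by prior nsVT, and state that it is not evidence that the score predicts nsVT.

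The groups should not be re-formed with the nsVT item set to no. That would move patients across the 4% cut-off and disturb the 17 and 17 design when 26 of 34 patients are already recruited.

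No new data are needed, and the article says that analysis has not begun. The cost is smaller denominators and wider confidence intervals. With 34% and 12.5% known, about 15 × 0.66 = 9.9 and 15 × 0.875 = 13.1 patients per group remain. If the group contrast were restricted to them, power by the same normal approximation would be about 0.68 (0.57 with 7% known in the low group), against 0.82 at 15 per group. With 16.9% known in the intermediate group it would be 0.78 to 0.86. The new-detection results should therefore be reported as estimates with confidence intervals, not as powered tests.
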